### On-site, supervised exercise program

The program will consist of progressive balance training, including postural orientation and anticipatory postural adjustments, sensory-motor activities, and strengthening exercises to enhance balance and postural control and reduce falls. Exercises in the standing position will be prioritised in order to target balance control. It has been found that programs that challenge balance and use a higher dose of exercises have greater relative effects on falls prevention [24]. In addition, exercises will be included to improve trunk flexibility, ankle mobility and proprioception. Exercises will be both static and dynamic, and will progressively increase in intensity to maximise strength and balance gains.

The group exercise protocol will comprise a fifteen minute warm-up followed by 45 minutes of a core set of balance and strengthening exercises performed in a standing position. The initial exercise dosage and level of difficulty will be individually prescribed by a physiotherapist after an assessment of each participant’s physical abilities. As gains are made, the exercises will be progressed in terms of number of repetitions to be completed, time to sustain a position, intensity of resistance used and task difficulty. For example, balance exercises will be progressed by using a narrower or unstable base of support, applying visual information deprivation, reducing upper limb support and using dual-task activities. The exercises will be demonstrated and supervised to ensure correct technique is used and the risk of falling is minimised. Initially participants will carry out the exercises next to a chair or to the wall, for immediate support in the event of loss of balance or if the participant feels insecure, however the use of upper limb support will be minimised when it is safe to do so to maximise the challenge to balance. The progression of exercises will also take into account the individual level of exertion required as measured by the Borg Rating of Perceived Exertion scale at the end of each exercise session.

The strengthening exercises will target ankle plantar flexors and dorsi flexors, knee extensors and hip abductors. Participants will use weight belts. Examples of the specific exercise to be included are heel raises in standing, forward and lateral step-ups onto a small block and sit to stand practice [27]. The balance exercises will consist of postural orientation exercises (weight bearing transfer in all directions of limits of stability, preferably using ankle motor strategy), static and dynamic balance exercises. The balance exercises will be included in a circuit protocol with different motor, sensory and cognitive tasks such as semi-tandem and tandem stance, stepping onto a block with alternate feet as quickly as possible, stepping and walking in different directions and at different velocities, negotiating obstacles and different surfaces, reaching for objects and making turns while walking. The complete exercise protocol will be available in a specific study manual and a training video.

### Home-based exercise program

Participants will be provided with a detailed booklet containing safety precautions, instructions and photographs of exercises for use in home exercise sessions. They will be instructed to do the exercises under the supervision of a relative or caregiver when possible, in a suitable place (with good lighting and ventilation) and using appropriate support (close to a table or chair, or the corner of a wall). At the first four group-based exercise sessions, additional instructions on how to carry out the home exercises will be provided to all intervention group participants. The exercises will be reviewed, if necessary, after each session until the last week of intervention. All necessary equipment to undertake the exercise program will be provided. Participants will be given an exercise diary for recording the frequency and number of repetitions of each exercise they perform as well as any minor adverse effects (e.g. muscle soreness, pain). The exercise diaries will be returned to the researchers at the 12 month re-assessment appointment. To avoid revealing study group allocation to the blinded assessor, exercise diaries will be placed in a locked box at the study site reception.

After a brief warm-up the home-based exercises will consist of similar exercises to those performed in the group sessions. Exercises will focus on strengthening of the ankle plantar flexors, knee extensors and hip abductors, performed in a standing position so that balance is challenged at the same time. Other exercises will include standing in a semi-tandem position, tandem walking and trunk righting. The progressions of home exercises will be concurrent with those done on-site in the group sessions. At the end of the intervention period, the participants will have reached at home the last progression level reached on-site and will be encouraged to maintain the dosage and progression level.

2. Educational/behavioural sessions addressing specific environmental and behavioural risk factors for falls will be delivered by trained health professionals. The 12 educational sessions will last for 40 minutes each and will use appropriate language for lay people. Audio-visual material will be used to support the verbal content when appropriate. Each meeting will consist of a brief introduction to the core topic for the day with supporting audio-visual or graphical material. This will be followed by group discussion to identify the beliefs, experiences and attitudes of participants regarding the discussion topic and any major barriers to the implementation of the suggested preventive strategies. In addition to discussing intervention strategies from the point of view of fall prevention, other benefits will be highlighted, such as for general health and improving or maintaining functional independence. The educational session will always end with a summary of the core messages of the session. Topics to be covered in the sessions are included in Table 1. The health care professional responsible for delivering the educational/behavioural sessions will attend a one-day training session and will receive a manual containing the specified core components of each session, learning strategies, goals to be achieved and messages to be delivered to participants.

3. A medical evaluation of modifiable risk factors not amenable to exercise will be performed by trained doctors, based on the currently available evidence [16]. The following risk factors will be addressed:

i. Postural hypotension

Participants with postural hypotension will be recommended to use pressure stockings and will receive counselling on associated behavioural factors, such as adequate fluid intake, sleeping with an elevated head, avoiding sudden changes in position and making circular movements with the feet before standing up. A review will be conducted into the use of medications that may contribute to postural hypotension such as antihypertensives, alpha agonists and tricyclic antidepressants and a contact with the primary care physician will be made to discuss any medication withdrawal. In regards to postprandial hypotension, participants will be encouraged to eat small, frequent meals, and to lie down after each meal.

ii. Visual impairment

Participants identified as having visual problems will be referred to an ophthalmologist. They will also be oriented in the proper use of bifocal or multifocal lenses while walking on the street and using stairs or ramps.

iii. The use of four or more medications or the use of psychotropic medication

A review of the risk-benefit of using specific medications will be undertaken, especially psychotropic and anti-hypertensive drugs and a contact with the primary care physician will be made to discuss any medication withdrawal. Counselling on avoiding self-medication will be provided.

iv. Undernutrition

Participants with a BMI lower than 22 kg/ m2 and/or a leg calf circumference under 31 cm will be instructed to increase their protein and calorie intake.

**Table 1 T1:** Educational topics covered during intervention

**Week no.**	**Session**
Week 1	Introduction to the Program for Prevention of Falls.
Week 2	Why do the elderly fall? Is falling normal in old age?
Week 3	The importance of exercise in strengthening muscles, improving balance and walking safely.
Week 4	What is risky behaviour? Is it normal to be afraid of falling? Which actions do I need to modify or avoid preventing falls?
Week 5	Medication and falls
Week 6	Is my home safe? How can I make it safer?
Week 7	How can I care for my feet? What is a safe shoe?
Week 8	Does food increase my risk of falling? How can I eat well?
Week 9	How good is my memory and attention span? What can I do to improve them?
Week 10	Do I see well? How important is my vision for safe indoor and outdoor mobility?
Week 11	Osteoporosis and the risk of fracture.
	How to get up from the floor after a fall.
Week 12	Why do I need to continue exercising?

### Outcomes

#### Data collection

Data will be collected from the baseline and follow-up physical assessments, monthly falls diaries, telephone contacts and medical and expert reports. The assessments will be conducted by independent, trained health care professionals who will not be providing the interventions and that will be unaware of the participants study group allocation. Participants will be instructed not to inform the assessors of their intervention status. Assessors will complete a questionnaire to assess their perception of the participants’ group allocation, in order to test the success of assessor blinding. The assessments will include questionnaires, physical examination and physical performance tests. All participants will undergo three assessments: the first at baseline prior to randomisation, the second and third at 6 and 12 months after commencement of the intervention respectively.

#### Primary outcome measures

The primary outcome will be the rate of falls and the proportion of fallers in 12 months after randomisation. Participants will receive instructions to fill in a monthly fall diary. They will receive telephone calls each month to ask for information regarding falls and their consequences, such as the mechanisms, environmental conditions, location (indoors or outdoors), activity during the fall and injuries sustained.

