**Methods/design:**

Multicentre parallel-group RCT involving 612 community-dwelling men and women aged 60 years and over, who have fallen at least once in the previous year. Participants will be recruited in multiple settings in Sao Paulo, Brazil and will be randomly allocated to a control group or an intervention group. The usual care control group will undergo a fall risk factor assessment and be referred to their clinicians with the risk assessment report so that individual modifiable risk factors can be managed without any specific guidance. The intervention group will receive a 12-week *Multifactorial Falls Prevention Program* consisting of: an individualised medical management of modifiable risk factors, a group-based, supervised balance training exercise program plus an unsupervised home-based exercise program, an educational/behavioral intervention. Both groups will receive a leaflet containing general information about fall prevention strategies. Primary outcome measures will be the rate of falls and the proportion of fallers recorded by monthly falls diaries and telephone calls over a 12 month period. Secondary outcomes measures will include risk of falling, fall-related self-efficacy score, measures of balance, mobility and strength, fall-related health services use and independence with daily tasks. Data will be analysed using the intention-to-treat principle.The incidence of falls in the intervention and control groups will be calculated and compared using negative binomial regression analysis.

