### Sample size calculation

A total of 612 participants (306 per group) will provide 80% power to detect as significant, at the 5% level, a 30% lower rate of falls (i.e. the primary outcome measure) for intervention group participants compared with control participants (i.e., IRR = 0.70). For the sample size calculation we used the gennbreg command in Stata and coefficients from previous studies: alpha (a measure of over-dispersion in the negative binomial regression model) was assumed to be 0.76 based on data from a previous trial [43]. We assumed the control group rate of falls would be 1 fall per person over the 12-month follow-up period. An average follow-up period of 11 months (rather than the planned 12 months) was used in these calculations to account for loss to follow-up.

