### Statistical analysis

The primary analyses will be conducted using the intention-to-treat principle. Fall data will be analysed using all randomised participants until they have died or have withdrawn from the study. Demographic and clinical characteristics at baseline will be summarized with descriptive statistics. The incidence of falls with 95% confidence intervals (CIs) in the two groups (intervention group and control group) will be calculated and compared using negative binomial regression analysis. The proportion of fallers in the two groups will be compared with the relative risk statistic. General linear models will be used to assess the effect of group allocation on the continuously-scored secondary outcome measures after adjusting for baseline scores. Logistic regression models will be used to compare groups on dichotomous outcome measures. Interactions between subgroup variables (past falls and mobility-related disability) and group allocation will be tested, and in the case of a significant interaction, the comparison between the intervention group and control group will be reported within the subgroups. Statistical analyses will be undertaken using the SPSS and Stata software packages. P < .05 will be considered statistically significant.

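### The article names two unordered primary outcomes in one place and one in another, so it does not fix what counts as success

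*Protocol article*

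**What the plan says.** The article describes the primary outcome in two ways.

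- **Two outcomes.** The Abstract (Methods/design) uses the plural: "Primary outcome measures will be the rate of falls and the proportion of fallers recorded by monthly falls diaries and telephone calls". The section Primary outcome measures repeats the pair: "The primary outcome will be the rate of falls and the proportion of fallers in 12 months after randomisation". Neither ranks them.
- **One outcome.** The Sample size calculation reads "A total of 612 participants (306 per group) will provide 80% power to detect as significant, at the 5% level", and the effect to be detected is "a 30% lower rate of falls (i.e. the primary outcome measure) for intervention group participants". No faller proportion, relative risk or power for fallers is given. The objective in the Abstract and the aim at the end of the Background also speak only of the rate of falls.

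The Statistical analysis section gives each outcome its own test. The incidence of falls "will be calculated and compared using negative binomial regression analysis". For the second outcome: "The proportion of fallers in the two groups will be compared with the relative risk statistic". One threshold covers everything: "P < .05 will be considered statistically significant". The section states no order, no division of the 5%, and no rule on whether one or both results are needed.

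The proportion of fallers does not appear under Secondary outcome measures. The risk of falling listed there is the QuickScreen score, so the proportion of fallers cannot be read as already secondary.

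**The concern.** How many primary outcomes a trial has, and which result makes it positive, is a protocol decision. Here the article fixes it in two incompatible ways. The stated 5% level and 80% power describe the whole trial only if the rate of falls is the sole or first-tested primary outcome, and the two places that define the outcomes do not say that.

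A split result is foreseeable. The proportion of fallers discards the number of falls per person and so has less power than the rate. The Background also cites a systematic review in which multifactorial programmes lowered fall rates while only exercise lowered the risk of falling. This programme is multifactorial but includes exercise, so that evidence does not predict its result, but it shows that the two outcomes can diverge. If they do, the article gives no answer to whether the trial succeeded.

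**Working it through.** **Inputs.** All from the Sample size calculation: 306 per group, dispersion k = 0.76, control rate 1 fall per 12 months, mean follow-up t = 11/12 year, IRR 0.70. Mean falls per person are therefore 0.917 (control) and 0.7 × 0.917 = 0.642 (intervention). Two assumptions are added: tests are two-sided, because sidedness is not stated, and everyone is followed for exactly 11/12 year.

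**1. The plan's own figure.** With the negative binomial Wald formula, the variance term is

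V = 1/0.917 + 1/0.642 + 2 × 0.76 = 1.091 + 1.558 + 1.520 = 4.169.

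For 80% power, n per group = (1.960 + 0.842)² × 4.169 / (ln 0.70)² = 7.849 × 4.169 / 0.1272, which rounds up to 258 (516 in total).

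At 306 per group, 0.3567 / √(4.169/306) = 3.056, and power = Φ(3.056 − 1.960) = 86.3%. The stated 612 is not reproduced. The plan used a simulation command whose settings are not shown, and the difference is conservative. Nothing below depends on it.

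**2. Proportion of fallers implied by the same model.** P(at least one fall) = 1 − (1 + kμ)^(−1/k).

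- Control: 1 − 1.697^(−1.316) = 50.1%
- Intervention: 1 − 1.488^(−1.316) = 40.7%
- Relative risk: 0.407/0.501 = 0.81

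For the log relative risk, the standard error is √[(0.499/0.501 + 0.593/0.407)/306] = 0.0895. Then 0.208/0.0895 = 2.325 and power = Φ(2.325 − 1.960) = 64%. A two-proportion formula gives 65%, and 438 per group for 80%.

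**3. Both tests together.** Simulated trials of 306 per group used gamma-Poisson counts, a negative binomial Wald test for the rate and a log relative risk Wald test for fallers, each two-sided at 5%. There were 20,000 trials with no effect and 8,000 with IRR 0.70.

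| Significant result on | No effect | IRR 0.70 |
|---|---|---|
| Rate of falls | 5.3% | 86.8% |
| Proportion of fallers | 4.9% | 63.6% |
| Either | 8.4% | 88.2% |
| Both | 1.8% | 62.2% |

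The two statistics correlate at 0.74 under no effect. Separate simulations gave 8.0% for either. As a cross-check, a bivariate normal gives 8.3% at correlation 0.70 and 8.1% at 0.75. The ceiling under independence is 1 − 0.95² = 9.75%. Varying the dispersion from 0.4 to 1.5 and the control rate from 0.7 to 1.5 (assumed ranges) gave 7.5% to 8.4%.

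**4. Direction of split results.** At IRR 0.70 the tests disagree in 26% of trials. The rate alone is significant in 86.8 − 62.2 = 24.6%, and fallers alone in 88.2 − 86.8 = 1.4%. With no effect, fallers alone are significant in 8.4 − 5.3 = 3.1%. Separate simulations put these last two figures at 1.6 to 1.7% and 2.9%.

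**The case against.** The strongest reply is that the intended lead outcome is clear. The objective, the aim and the sample size all name the rate of falls, and the only comparison the Abstract describes is the negative binomial one. A testing order is the kind of detail an analysis plan often supplies, and that plan is not shown. The two outcomes count the same events and correlate strongly, and a win on fallers alone would be rare.

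Much of this stands. The missing order, taken alone, would be no finding. The rarity of a fallers-only win limits the practical harm. The emphasis on the rate supports the fix proposed below. What remains is a contradiction in the stated text: one section defines two primary outcomes and another refers to one. An analysis plan could add an order, but the two sections would still disagree.

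Three stronger readings are tempting, and the article does not support them.

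- *The trial has an 8% type I error.* That needs a rule that either outcome suffices, and no section states one. While the rule is open there is no single error rate.
- *The 80% power claim is wrong because both outcomes must succeed.* The claim is made for the rate only, and on the stated inputs the rate exceeds it.
- *The plan lets the sponsor claim success on whichever outcome is significant.* No text grants this. The text only fails to exclude it.

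**Conclusion.** The point holds as a contradiction over what is primary, with the success rule left open. Its size depends on how the gap is filled:

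- **Either outcome suffices:** familywise error about 8% instead of 5%. Roughly half of that, 4.1%, would favour the intervention.
- **Both required:** error about 2%, joint power about 62%.
- **Rate sole or first:** error 5%, power about 86% on the stated inputs.

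The commonest split at the design effect, in about a quarter of trials, is a significant rate with a non-significant faller proportion. That is the case the article most needs to settle.

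The error figures rest on two-sided tests and equal follow-up, and changed little over the assumed ranges. The figures of 64% (fallers) and 62% (both) are less secure. They also assume that the effect on fallers arises entirely from the negative binomial model, and the article gives no faller proportion against which to check this.

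**What to change.** Name the rate of falls, as the negative binomial IRR over 12 months from randomisation, as the only primary outcome. This agrees with the objective, the aim and the sample size. Make the proportion of fallers the first secondary outcome, tested at 5% only if the rate comparison is significant, which holds these two tests at 5% overall. Use the same wording in the Abstract, Primary outcome measures and Statistical analysis, and carry it into the analysis plan and the registration.

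The cost is wording, with no added participants or data. The trial was still recruiting when the article was published, so the rule could be set before outcomes are known. The downside is that a significant faller proportion alone could not be claimed as primary success.

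If the investigators want both outcomes as primary, testing each at 0.025 is acceptable. Power for the rate is then Φ(3.056 − 2.241) = 79%, close to the planned 80%. For fallers it is Φ(2.325 − 2.241) = 53% under the model above. The article should then say that success on either outcome suffices.

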#### Secondary outcome measures

Secondary outcome measures will be the risk of falling, fall-related self-efficacy score, measures of balance, mobility and strength, health services use and difficulty with daily tasks. These outcome measures are described below.

**Fall-related self-efficacy** will be assessed with the *Falls Efficacy Scale International*[28], translated and adapted in its Brazilian version [29], which consists of a questionnaire with16 activities in which the participant rates, on a 4-point scale their degree of concern about the possibility of falling while carrying out the activities. It measures their degree of self-efficacy to avoid falling.

**Balance mobility and strength** will be measured by the: *Berg Balance Scale*[30-32], *Alternate Step test*[31], *Sit to stand Test*[33,34]*and Hand grip strength*[35,36]. The Berg Balance Scale consists of 14 common tasks involving static and dynamic balance, such as reaching, turning, moving, standing and getting up. Ability to perform the tasks is graded from 0 to 4, with an overall maximum score possible of 56 points, and higher scores indicating better balance. The *Alternate Step test*[31] requires the participant to stand in front of an 18-cm high step or stool and at a verbal command the participant taps the whole foot (shoes removed) onto the step, and alternates with the right and left feet, for a total of eight repetitions as quickly as possible. The time taken to complete the task is the score. The *Sit-to-stand test* will be used to primarily assess lower limb strength. There will be a pre-test which involves the patient moving from sitting in a chair to a standing position without the assistance of their hands. If the subject can perform this movement, they will be instructed to repeat the test, as quickly as possible, five times consecutively with their upper arms crossed over their chest. The time taken to perform this task will be recorded. *Hand Grip strength* will be assessed using a portable hand dynamometer (SAEHAN® model SH5001). The participant will be seated with their shoulder in a neutral position and their elbow flexed at 90°.Three attempts will be performed alternately in each hand; the mean of the three measures will be recorded.

**Fall risk** will be assessed using the *QuickScreen Clinical Falls Risk Assessment*[37], a validated instrument consisting of five physical performance items, two questions about medications and one about previous falls. An individual’s estimated fall risk will be considered to have decreased if, upon retest, they have moved down to the next level in the risk categories proposed by Tiedemann et al. [37]. The risk categories and their associated probabilities of future falls are as follows: for 0–1 QuickScreen items, the probability of falling is 7%, for 2–3 items the probability of falling is 13%, for 4–5 items the probability of falling is 27% and for 6 or more items the probability of falling is 49%.

**The level of *****difficulty with daily tasks*** will be assessed using the Brazilian OARS Multidimensional Functional Assessment Questionnaire (BOMFAQ) adapted from the Older Americans Resources and Services (OARS) [38] instrument that measures self-reported difficulty while performing 15 daily activity tasks: eight activities of daily living : lying down and getting up from bed, eating, combing hair, dressing, bathing, walking on a uneven surface, getting to the toilet in time, cutting toenails and seven instrumental activities of daily living: taking medications, climbing stairs, walking near home, preparing meals, taking public transport, shopping and cleaning the house, hierarchically organized. The number of activities performed with difficulty will be summed and categorized as follows: 0, 1 to 3, 4–6 or 7 or more activities.

**Services use** will be measured by the number of fall-related visits to emergency departments and hospitalisations (frequency and duration) per participant.

**Compliance** with the home exercise program (frequency and duration) will be recorded in a home exercise diary. Adverse side effects will be measured with an adverse events form, including stiffness, pain, fatigue, etc. At the end of the follow-up period participants will be asked to identify reasons for non-adherence on the home-based exercise program.

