### Participants

Community-dwelling men and women aged 60 and over who have fallen at least once in the last 12 months will be included. A fall will be defined as “an unexpected event in which the participants come to rest on the ground, floor, or lower level.” Participants will be asked to answer the question: “In the past 12 months, have you had any fall including a slip or trip in which you lost your balance and landed on the floor or ground or lower level?” [26].

At initial contact potential participants will be screened by telephone to ensure they have fallen at least once in the past 12 months and will be able to attend the evaluation centre once a week for 12 weeks. If there is an affirmative answer to both questions, the person will be invited to attend the evaluation centre to be assessed for eligibility.

Participants will be excluded if they have:

• A previous diagnosis of dementia or a cognitive decline that prevents the understanding of simple instructions or guidelines;

• A previous stroke with a severe neurological impairment, such as loss of strength, and perceptual or language limitations;

• A progressive neurological disease (e.g. severe Parkinson’s disease);

• A severe visual deficiency;

• Any acute illness that the physician considers as an exercise contra-indication (e.g. uncontrolled angina, acute coronary disease);

• An acute vertigo or dizziness less than3 months duration;

• Inability to maintain a standing position, even with the use of a walking aid or other device.

Participants will also be excluded if they unable to communicate due to an aphasia, severe hearing loss even with the use of hearing aids or those who do not have mastery in Portuguese language. People will also be excluded from participation if they are engaged in a regular exercise program that is likely to challenge balance, including physical therapy, with a frequency of equal to or more than twice a week such as: muscle strengthening, balance or gait exercise, Tai Chi and Yoga. People will not be excluded if their regular exercise regime is limited to walking, water-based exercise or any other form of therapy that does not include the exercises described above (e.g., thermotherapy, spine and shoulder exercises, etc.).

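### The QuickScreen outcome is reduced to a yes/no band drop that discards information and may partly repeat the falls outcome; BOMFAQ is banded in a way that the named models do not cover

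*Protocol article*

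**What the plan says.** Under Secondary outcome measures, the protocol article describes QuickScreen as an instrument "consisting of five physical performance items, two questions about medications and one about previous falls", so the score runs from 0 to 8. It groups the score into four bands (0–1, 2–3, 4–5, and 6 or more) with attached fall probabilities of 7%, 13%, 27% and 49%. It then sets the outcome rule: "fall risk will be considered to have decreased if, upon retest, they have moved down to the next level in the risk categories".

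Two other sections bear on the falls item. Participants restricts entry to people "who have fallen at least once in the last 12 months will be included". Primary outcome measures states: "The primary outcome will be the rate of falls and the proportion of fallers in 12 months after randomisation". Data collection places the retests at 6 and 12 months after the intervention starts. The article gives neither the look-back period of the QuickScreen falls item nor whether it is re-scored at retest.

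For daily tasks, BOMFAQ covers 15 activities. "The number of activities performed with difficulty will be summed and categorized as follows": 0, 1–3, 4–6, and 7 or more. Statistical analysis names a general linear model, adjusted for baseline, for continuously scored secondary outcomes, and logistic regression for dichotomous ones.

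**The concern.** There are two separate issues.

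The first needs no assumption. A count collected on every participant is turned into a binary band drop, so whether a given change registers depends on where in a band the person started. This costs precision and treats equal changes unequally. BOMFAQ is cut in the same way, into four ordered categories that are neither continuous nor dichotomous.

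The second is conditional. If the falls item covers roughly the last 12 months and is asked again at 12 months, everyone is positive at entry because of the eligibility rule, and the item clears for those who do not fall during follow-up. A participant could then be classed as having lower fall risk with no change in any physical or medication item. A positive result on this outcome would look like independent support for the primary result, when part of it is the same falls counted again.

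**Working it through.** The protocol states no expected value for this outcome, so there is no figure of its own to reproduce. The check enumerates the rule and then applies the sample-size inputs to the falls item.

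**Step 1. Band rule, scores 1 to 8** (reaching any lower band is counted as a decrease)

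| Baseline score | Loses 1 item | Loses 2 items |
|---|---|---|
| 1 | not counted | not possible |
| 2 | decreased | decreased |
| 3 | not counted | decreased |
| 4 | decreased | decreased |
| 5 | not counted | decreased |
| 6 | decreased | decreased |
| 7 | not counted | decreased |
| 8 | not counted | not counted |

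A change from 2 to 1 is a success, while 8 to 6 is not. A score of 1 is already in the lowest band and cannot succeed. Because the outcome is yes/no, a participant who moves up a band is recorded the same as one who does not move.

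**Step 2. How often the falls item would clear**

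Inputs from Sample size calculation: control rate 1 fall per person over 12 months, rate ratio 0.70, negative binomial over-dispersion k = 0.76. Assumptions: 12-month look-back, re-scored at the 12-month retest.

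P(no fall) = (1 + k × mean)^(−1/k)

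- Control: (1 + 0.76 × 1)^(−1/0.76) = 1.76^(−1.316) = 0.475
- Intervention: (1 + 0.76 × 0.7)^(−1/0.76) = 1.532^(−1.316) = 0.570

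The complements, 52.5% and 43.0%, are the proportions of fallers (relative risk 0.82). Under these assumptions the item therefore carries the same contrast as the second primary measure. The match is approximate, because the primary period runs from randomisation and the retests are timed from the start of the intervention.

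**Step 3. Effect on the outcome if nothing else changes**

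From Step 1, losing one item matters only at baseline scores of 2, 4 or 6. The document does not give the share of participants at those scores, so 25%, 50% and 75% are taken as an assumed range. Clearing is treated as independent of baseline score.

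| Share at 2, 4 or 6 | Control (share × 0.475) | Intervention (share × 0.570) | Gap, points | Odds ratio |
|---|---|---|---|---|
| 25% | 11.9% | 14.3% | 2.4 | 1.23 |
| 50% | 23.8% | 28.5% | 4.8 | 1.28 |
| 75% | 35.6% | 42.8% | 7.1 | 1.35 |

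With 306 per group, the power to find these gaps significant at the two-sided 5% level is about 14%, 27% and 44%.

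**Step 4. The 6-month retest**

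A 12-month look-back at 6 months also reaches about 6 months before the programme. Let q be the share with no fall in those earlier 6 months (not given; 0.2 to 0.5 assumed, and independent of later falls). P(no fall in 6 months) is 0.655 for controls (mean 0.5) and 0.733 for the intervention group (mean 0.35). The item clears in q times these values: 13.1% v 14.7% at q = 0.2, and 32.7% v 36.7% at q = 0.5. The overlap is weaker, so the same label would mean different things at the two retests.

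**Step 5. BOMFAQ**

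A count of 0 to 15 has 16 possible values. The top band (7 to 15) holds nine of them. Going from 15 to 7 tasks leaves the band unchanged, while going from 4 to 3 changes it. Four ordered bands are the natural input for neither model named in Statistical analysis.

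**The case against.** The strongest reply is that the overlap rests on something the article does not say. If the item asks about any past fall, or is carried forward from baseline, it is constant and nothing is repeated. With a look-back shorter than 12 months, not everyone is positive at entry. Item scoring is also the kind of detail an article leaves to the full protocol. This stands: the overlap must be stated as conditional, and its absence from the article is not in itself a fault. The 12-month reading is natural because the entry question uses that window, but it remains a reading.

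A reader might also infer that the comparison is biased, or that regression from the entry criterion would produce a spurious benefit. The documents do not support that. The item behaves alike in both randomised arms, and the gaps in Step 3 arise only because a true rate ratio of 0.70 was put in. With no effect on falls, this item creates no difference. Even with that effect, the power figures show that the item alone would usually not reach significance.

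Further points carry some weight. The protocol presents the measure as an estimate of fall risk, not as a measure of physical function. Berg balance, alternate step, sit-to-stand and grip strength are reported separately and contain no falls item. The bands are pre-specified and published, and dropping an item from an instrument described as validated is debatable. That is a reason to keep the full score as the main analysis and to use the seven-item version for sensitivity only.

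On BOMFAQ, a method for ordered categories could be specified in the analysis plan. That would answer the mismatch with the named models, but not the loss of information from banding.

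**Conclusion.** The point holds in two parts of different strength.

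Without any assumption, the QuickScreen rule discards information and treats equal changes unequally, and the BOMFAQ bands lose detail and match neither named model. This is a weakness of analysis choice in secondary outcomes, not an error or a contradiction in the design.

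Conditionally, on a 12-month look-back with re-scoring at 12 months, part of the QuickScreen outcome repeats the primary proportion of fallers. The contribution of that item alone would be a gap of about 2 to 7 percentage points, given the sample-size inputs, the assumed 25% to 75% at scores of 2, 4 or 6, and independence of clearing from baseline score. The consequence is limited to interpretation: a favourable result should not be read as evidence independent of the falls outcome.

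**What to change.** - Analyse the QuickScreen item count (0–8) and the BOMFAQ count (0–15) with the baseline-adjusted general linear model already planned. Keep both sets of bands for description.
- State the look-back period of the previous-falls item and whether it is re-scored at 6 and 12 months.
- Add a sensitivity analysis of the seven-item QuickScreen count without the falls item, so that readers can see how much of any effect lies outside the falls outcome.

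The cost is analysis-plan wording; no new data, visits or participants are needed. The published risk bands become descriptive, which loses some clinical readability, and a linear model on a short bounded count is approximate. Trial status reports that recruitment is still under way, so the change can be settled before any outcome comparison is seen.
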